## Sample Size

**Sample size justification:** The sample of 30 will provide typical precision for a pilot study of feasibility and acceptability outcomes. Specifically, we will be able to estimate the mean of continuous outcomes within margins of sampling error (MSEs; half-widths of 95% confidence intervals) of 0.37 standard deviations (SD) overall, and 0.55 SDs within arm; percentages will be estimated within MSEs of 11-18 points overall, and 15-25 points within arm, depending on the sample value. In designing the full-scale trial, these exploratory results will be cautiously interpreted in the light of confidence intervals, plausibility, and prior results.

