| Target Population: | Hepatitis C virus (HCV), Genotype 1 infected adults |
| Duration of Treatment: | Subjects will be treated for 8 weeks |
| Objectives: | The primary objectives of this study are as follows:   1. To assess the feasibility of treating persons who actively inject drugs (PWIDs) for HCV with Ledipasvir/Sofosbuvir Fixed-Dose Combination (LDV/SOF) by modified directly observed therapy (mDOT) versus unobserved dosing, with motivational interviewing (MI) adherence counseling, as measured by recruitment and retention rates, overall and by arm. 2. To evaluate the acceptability of mDOT versus unobserved dosing, with MI adherence counseling, among PWIDs treated with LDV/SOF, as determined by mDOT and MI participation rates, medication adherence rates and the proportion of subjects that complete therapy, overall and by arm. 3. To assess through in-depth, semi-structured qualitative interviews, the challenges required for mDOT and unobserved dosing, and identify key factors affecting treatment adherence to LDV/SOF for PWIDs.   The exploratory objectives of this study are as follows:   1. To assess end-of-treatment response and sustained virologic response (SVR), as determined by the proportion with undetectable HCV RNA at week 8 and post-treatment week 12, by arm. 2. To assess adherence to treatment by SOF metabolite levels, by arm, as needed based on SVR rates and medication adherence data. 3. To assess drug use behaviors before and after HCV treatment. 4. To assess HCV relapse and reinfection at post-treatment week 36 among participants achieving SVR. 5. To evaluate demographic, behavioral and HCV strain correlates of adherence and SVR. 6. To characterize the social and injector networks of participants in preparation for a subsequent full TasP trial. |
| Study Design: | Thirty subjects will be enrolled 2-to-1 in one of the following two treatment arms:  **Group 1:** Modified Directly Observed Therapy (N=20)   - LDV/SOF tablet (LDV 90mg/SOF 400mg) observed daily dosing (modified for non-observed Saturday and Sunday dosing) for 8 weeks   **Group 2:** Unobserved Dosing (N=10)   - LDV/SOF tablet (LDV 90mg/SOF 400mg) provided weekly (7 tablets) for unobserved daily dosing for 8 weeks |

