| Statistical Methods: | **Aim 1**: To assess the feasibility of treating active PWIDs for HCV with LDV/SOF by mDOT versus unobserved dosing, as measured by recruitment and retention rates overall and by arm. We will calculate the following feasibility measures: 1) proportion of those eligible among those screened; 2) proportion enrolled among those eligible; and 3) study retention and completion rates, overall and by arm. Process measures (e.g., visit length) and reactions to study procedures will also be assessed. Descriptive statistics will be presented with 95% confidence intervals, to help in interpretation. Between-group differences in retention and completion will be assessed using Fisher’s exact and Wilcoxon tests. We will also calculate Kaplan-Meier curves for time to dropout, by group, and test for differences using the log-rank test.  **Aim 2**: To evaluate the acceptability of mDOT versus unobserved dosing, the percent of treatment medication adherence to LDV/SOF, as measured by the percent of doses taken overall (observed and unobserved), will be assessed using DOT doses and weekend Wise Pill data for the mDOT arm, and WisePill data for the unobserved dosing arm. Other outcomes of interest will include completion of therapy, patterns of adherence, and time to stopping medication. Concordance of the various adherence measures will be examined using weighted Kappa and intraclass correlations. Between-arm differences will be assessed using Fisher’s exact and Wilcoxon tests for outcomes measured once, and GEE models for repeated outcomes. We will also use GEE models to compare WisePill openings and pill counts, accounting for between-arm differences in expected frequency.  Sample size justification: The sample will provide typical precision for a pilot study of feasibility and acceptability outcomes. Specifically, we will be able to estimate the mean of continuous outcomes within margins of sampling error (MSEs; half-widths of 95% confidence intervals) of 0.37 standard deviations (SD) overall, and 0.55 SDs within arm; percentages will be estimated within MSEs of 11-18 points overall, and 15-25 points within arm, depending on the sample value. In designing the full-scale trial, these exploratory results will be cautiously interpreted in the light of confidence intervals, plausibility, and prior results.  **Aim 3**: To assess through in-depth, semi-structured qualitative interviews, the challenges with time intensity required for mDOT versus unobserved dosing, and identify key factors affecting treatment adherence for PWIDs treated with LDV/SOF. Transcribed semi-structured interviews conducted at the End-of-Treatment (week 8 or early termination) visit will be imported into Atlas.ti, a qualitative research software program. We will utilize two qualitative analytic methods to interpret data. First, content analysis will allow us to focus on answering study questions regarding experiences with LDV/SOF treatment and DOT strategies, and opinions on challenges to achieving consistent adherence to treatment. *A priori* themes of interest primarily focused on the time-intensity required for this treatment plan and based upon the team’s experience with HCV treatment among PWIDs will be developed and used as the first codebook with which data are coded. Second, thematic analysis with open coding will allow themes to emerge from the data. A coding system will be developed using an iterative process. In the initial phase, we will review all transcripts and field notes to become familiar with the data, and the analytic team will make notes of their observations and potential codes for use in the initial analysis meeting. Then a codebook, consisting of the code definition and inclusion and exclusion criteria, will be created to aid analysis. In addition to predetermined HCV treatment dimensions, additional codes will be developed independently by each analytic team member through an inductive process of identifying themes that emerge from the data. Group analysis meetings will be held to compare independently developed codes for similarity and further definition. A consensus will be reached regarding each code, its application and definition. To ensure consistency, a codebook and dictionary will be developed with universal definitions for each code.  *Inter-rater reliability*: To ensure reliability and validity in the open-ended component of the in-depth interviews analysis, we will implement a verification strategy to ensure self-correction throughout the analysis process. The two coders will assess inter-rater reliability by calculating the correlation between a set of ratings done by two independent raters for the initial set of 3-6 transcripts, and then again on the next set of 6 transcripts. After each inter-rater reliability assessment, the codebook and codes will be revised based on reconciliation of findings done between coders. Inter-rater reliability will be assessed as a team twice during the analysis process and again at the end of analysis as a post-hoc evaluation of reliability and validity. This evolving analysis process will ensure high quality of research decisions, the rationale behind decisions, and the responsiveness of investigators to the data. Once the codebook is developed and verified all remaining transcripts will be coded. Further meetings will be held to discuss any differences in coding and to ensure consistency in the application of codes.  Final analysis will begin with data reduction, then display, analysis and conclusion drawing using a conceptual framework in which hypothesized factors affecting adherence are assessed and unanticipated findings are identified. The analytic team will work from the coded data to merge findings into a final summary and a consensus of major themes, relationships between themes, and ranking of items of most importance to adherence. This method of data reduction encompassing both site and team based analysis creates a robust iterative process through which the data is thoroughly discussed and analytical consensus achieved. *Atlas.ti* software will be used to both code and develop data displays used in the analysis for this study.  **Exploratory Aims**: While we recognize the small sample size limits our ability to draw firm conclusions from exploratory analyses, the paucity of data for this treatment approach allows for hypothesis-generating results.  *End-of-treatment response and SVR*: We will compare the proportion of participants with undetectable HCV RNA at week 8 and post-treatment week 12 between arms using Fisher’s exact tests.  *Acceptability based on drug levels*: If SVR, retention and/or medication adherence data suggestion medication compliance issues, we may compare SOF metabolite–positivity rates will be calculated by week in both arms; between-group differences will be compared using GEE models for repeated outcomes.  *HCV relapse and reinfection*: Among participants who achieve SVR, we will determine the proportion who experience HCV relapse and reinfection at post-treatment week 36, overall and by arm, with exact 95% confidence intervals. We will sequence HCV RNA in such cases to establish if the event represents relapse versus reinfection.  *Social and injection network analyses to inform a subsequent full TasP trial*: We will characterize injector network sizes at baseline and follow-up. Newman’s method will be used to calculate assortativity coefficients, a measure of the degree of demographic and risk behavior similarity within networks. These findings will help us determine whether a full efficacy trial should use targeted sampling strategies to ensure diversity in network sizes, and whether randomization should be stratified by one or both of these factors in future trials.  **Other Exploratory Outcomes**:  *Drug use behaviors before and after HCV treatment*: Recent data suggest significant changes in drug use behaviors after HCV diagnosis: serosorting with other HCV-positive PWIDs and a sustained reduction in drug use. We will assess these behaviors at baseline and follow-up for preliminary estimates of the possible impact of HCV treatment on these behaviors. ANCOVA and conditional logistic models will be used for continuous and binary outcomes respectively.  *Correlates of Adherence and SVR*: We will explore demographic, behavioral correlates of medication adherence using GEE models for repeated measures. In addition, we will explore demographic and behavioral correlates of SVR using Fisher exact tests and exact logistic regression. |

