### Enrollment Visit

Enrollment tests and procedures will be completed prior to enrollment and dosing/dispensing of study drug.

Enrollment visit will include a urine drug screen, urine β‑hCG (females of childbearing potential only), vital signs, randomization to study arm, motivational interviewing–based counseling pertaining to risk reduction and medication adherence, administration of the Audio Computer Assisted Self Interview (ACASI), and medication dispensation (unobserved dosing) or first directly observed dosing (mDOT).

Subjects will be randomized 2:1 to mDOT (n=20) or unobserved dosing (n=10) using permuted blocks of randomly selected sizes 2 and 4 generated using a STATA computer program. Staff members who have no contact with study participants will enclose and seal treatment allocation cards in sequentially numbered opaque envelopes to correspond with the randomization sequence. As a participant is enrolled, the envelope that corresponds with their sequence will be opened to reveal their randomized treatment condition.

mDOT subjects will receive a 10-trip Muni card to cover weekly round-trip transportation to study site and the unobserved dosing arm will receive a weekly two-trip Muni card to cover round-trip transportation to study site. These cards will be dispensed at weekly visits only so as to avoid directly compensating participants for attending daily visits.

Subjects will be compensated $20 for the enrollment visit.

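### The single within-arm precision (0.55 SD; 15-25 points) fits arms of 15 and is not the precision of either planned arm: it is too wide for the 20-person arm and too narrow for the 10-person arm

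*Protocol*

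**What the plan says.** Section 9.7 (Sample Size) justifies the sample by precision alone: "The sample of 30 will provide typical precision for a pilot study of feasibility and acceptability outcomes". It defines the margins as half-widths of 95% confidence intervals. For means it gives 0.37 SD overall, and it continues: "0.55 SDs within arm; percentages will be estimated within MSEs of 11-18 points overall, and 15-25 points within arm", depending on the sample value. The synopsis (Statistical Methods) carries the same figures, including "0.37 standard deviations (SD) overall, and 0.55 SDs within arm". Neither place says which arm the within-arm figures describe.

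The arms are unequal by design. Section 6.2.2 (Enrollment Visit) states: "Subjects will be randomized 2:1 to mDOT (n=20) or unobserved dosing (n=10"). The synopsis (Study Design) agrees: "Thirty subjects will be enrolled 2-to-1 in one of the following two treatment arms", with 20 and 10 listed for the two groups. Arms of 15 are described nowhere.

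**The concern.** A single within-arm figure can be right for both arms only if the arms are the same size. Here one is twice the other, so the stated margin must be wrong for at least one of them.

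Precision is the only argument offered for the sample size; no power calculation is given. Retention, study completion, medication adherence and completion of therapy are primary endpoints reported by arm (Section 9.1.2), and the results are meant to inform a full-scale trial. Someone planning that trial from Section 9.7 would expect more certainty about the unobserved-dosing arm than ten people can give.

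**Working it through.** **Inputs.** Total 30 (Section 9.7). Arms 20 and 10 (Section 6.2.2 and synopsis). Margin = half-width of a two-sided 95% interval (Section 9.7). The protocol does not name the formulas or the range of percentages, so both were identified from the overall figures. The range of 10% to 50% (equivalently 50% to 90%) is therefore an assumption.

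**Formulas.**
- Means, in SD units: t(0.975, n−1)/√n.
- Percentages (Wald): 1.96 × √(p(1−p)/n), at p = 0.10 and p = 0.50.

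**Step 1: reproduce the overall figures (n=30).**
- Means: 2.045/√30 = 0.373 SD (stated 0.37). A normal quantile would give 0.358, so t was used.
- Percentages: 1.96 × 0.3/√30 = 10.7 points and 1.96 × 0.5/√30 = 17.9 points (stated 11-18).

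Both reproduce.

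**Step 2: find the single arm size that returns the within-arm figures.**
- n=15: 2.145/√15 = 0.554 SD; 15.2 to 25.3 points. This matches the stated 0.55 SD and 15-25 points.
- n=14 gives 0.577 SD and n=16 gives 0.533 SD. Neither rounds to 0.55.

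**Step 3: apply the same formulas to the planned arms.**

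| | Means (SD) | Percentages (points, p = 10% to 50%) |
|---|---|---|
| Stated, within arm | 0.55 | 15-25 |
| mDOT, n=20 | 2.093/√20 = 0.468 | 13.1-21.9 |
| Unobserved, n=10 | 2.262/√10 = 0.715 | 18.6-31.0 |

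For the 10-person arm, 0.715/0.55 = 1.30, so the margin for means is about 30% wider than stated. The widest percentage margin is 31 points against a stated 25.

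**Step 4: does another interval method rescue the small arm?** At n=10:
- normal quantile for means: 0.62 SD;
- Wilson, at 1/10 and 5/10: 19.3 to 26.3 points;
- Clopper-Pearson, at 1/10 and 5/10: 22.1 to 31.3 points.

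All exceed the stated figures, although Wilson comes close at the upper end.

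**Step 5: the extra subject.** The section on number of subjects allows a 31st participant. If that person is in the small arm, n=11 gives 0.67 SD and 18-30 points. If in the large arm, n=21 gives 0.46 SD and 13-21 points. The conclusion does not change.

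**The case against.** **The mDOT arm does better than stated.** This stands. A reader might infer that the trial as a whole cannot deliver the stated precision. The protocol's own numbers do not support that: at n=20 the margins are narrower than claimed, and only the 10-person arm falls short.

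**The figure may be an average over the two arms.** A simple average does not fit: (0.468 + 0.715)/2 = 0.59 SD. A size-weighted average does: (2 × 0.468 + 0.715)/3 = 0.550 SD, and for percentages 15.0 to 24.9 points. So it cannot be said that only arms of 15 yield the stated numbers. A reader might also take the match at n=15, together with block sizes of 2 and 4 that cannot hold a 2:1 ratio within a block, as proof of a carry-over from a 1:1 design. That is an inference about origin which the protocol does not confirm. Neither origin repairs the text: no averaging is stated, and an average is not the precision of either arm.

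**Little depends on it.** This largely stands. Thirty subjects are already enrolled, and the figures feed no power claim, stopping rule or go/no-go threshold. Section 9.5.1 promises descriptive statistics with 95% confidence intervals, and these will reflect the real arm sizes whatever Section 9.7 says. Two of the primary endpoints are overall only and one is qualitative, so not every primary result is read by arm.

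**The size of the percentage error depends on the method.** This also stands. The worst case for n=10 is 31 points under Wald or Clopper-Pearson but about 26 under Wilson. The shortfall for means, and at the low end of the percentage range (19 or more against 15), remains under every method tried.

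**Conclusion.** The within-arm statement is wrong as written. One pair of figures is given for two arms of different size, and it describes neither. By the formulas that reproduce the overall figures, the claim is too pessimistic for mDOT and too optimistic for unobserved dosing, where the margin for means is about 30% wider than stated and the margins for percentages are 19-31 points.

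This rests on the planned 20 and 10, and for percentages on Wald intervals with proportions from 10% to 50%. The result for means needs no assumption about proportions.

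It is an error of arithmetic in the sole justification for the sample size. It should not be read as showing that the sample is inadequate or that the reported results will be wrong; the document supports neither.

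**What to change.** In Section 9.7 and in the synopsis, replace the within-arm figures with arm-specific ones and name the method and the range of proportions:

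- mDOT (n=20): 0.47 SD; 13-22 points.
- Unobserved dosing (n=10): 0.72 SD; 19-31 points.

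These percentage margins are Wald half-widths for proportions of 10% to 50%, the same basis as the overall 11-18 points. If exact intervals will be reported, quote Clopper-Pearson half-widths instead: about 15-23 points for n=20 and 22-31 for n=10. The overall range should then move to the same basis, about 12-19 points (3/30 to 15/30). Do not print margins from one method while promising intervals from another.

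Confirm the realised arm sizes first, given the stated block sizes and the possible 31st participant, and use those if they differ from 20 and 10.

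The change is one sentence in two places and needs no extra patients. Its only cost is a less favourable stated precision for the small arm.

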# RESPONSIBILITIES

## Investigator Responsibilities

### Good Clinical Practice

The investigator will ensure that this study is conducted in accordance with the principles of the Declaration of Helsinki (as amended in Edinburgh, Tokyo, Venice, Hong Kong, and South Africa), International Conference on Harmonisation (ICH) guidelines, or with the laws and regulations of the country in which the research is conducted, whichever affords the greater protection to the study subject.

The investigator and all applicable subinvestigators will comply with 21 CFR, Part 54, 1998, providing documentation of their financial interest or arrangements with Gilead, or proprietary interests in the investigational drug under study. This documentation must be provided prior to the investigator’s (and any subinvestigator’s) participation in the study. The investigator and subinvestigator agree to notify Gilead of any change in reportable interests during the study and for 1 year following completion of the study. Study completion is defined as the date when the last subject completes the protocol-defined activities.

### Institutional Review Board (IRB) Approval

The investigator (or sponsor as appropriate according to local regulations) will submit this protocol, informed consent form, and any accompanying material to be provided to the subject (such as advertisements, subject information sheets, or descriptions of the study used to obtain informed consent) to an IRB. The investigator will not begin any study subject activities until approval from the IRB has been documented and provided as a letter to the investigator.

Before implementation, the investigator will submit to and receive documented approval from the IRB any modifications made to the protocol or any accompanying material to be provided to the subject after initial IRB approval, with the exception of those necessary to reduce immediate risk to study subjects.

### Informed Consent

Study staff are responsible for obtaining written informed consent from each individual participating in this study after adequate explanation of the aims, methods, objectives, and potential hazards of the study and before undertaking any study-related procedures. The investigator will use the most current IRB approved consent form for documenting written informed consent. Each informed consent will be appropriately signed and dated by the subject or the subject’s legally authorized representative and the person conducting the consent discussion, and also by an impartial witness if required by IRB or by local requirements. The consent form will inform subjects about sample retention and use of retained samples.

### Confidentiality

The investigator will assure that subjects’ anonymity will be strictly maintained and that their identities are protected from unauthorized parties. Only subject initials, date of birth, and a unique identifier (as allowed by local law) will be recorded on any form or biological sample submitted to the Sponsor, IRB, or laboratory. Laboratory specimens will be labeled in such a way as to protect subject identity while allowing the results to be recorded to the proper subject. Refer to specific laboratory instructions. NOTE: If given signed permission by the subject the investigators keeps a locator form showing names, date of birth and addresses for all subjects screened and for all subjects enrolled in the trial. Subject data will be processed in accordance with all applicable regulations.

### Study Files and Retention of Records

The investigator will maintain adequate and accurate records to enable the conduct of the study to be fully documented and the study data to be subsequently verified. These documents should be classified into at least the following two categories: (1) investigator’s study file, and (2) subject clinical source documents.

The investigator’s study file will contain the protocol/amendments, CRF and query forms, IRB and governmental approval with correspondence, informed consent, drug records, staff curriculum vitae and authorization forms, and other appropriate documents and correspondence.

The required source data should include sequential notes containing at least the following information for each subject:

- Subject identification (name, date of birth, gender);
- Documentation that subject meets eligibility criteria, ie, history, physical examination, and confirmation of diagnosis (to support inclusion and exclusion criteria);
- Documentation of the reason(s) a consented subject is not enrolled
- Participation in study (including study number);
- Study discussed and date of informed consent;
- Dates of all visits;
- Documentation that protocol specific procedures were performed;
- Results of efficacy parameters, as required by the protocol;
- Start and end date (including dose regimen) of study drug, including dates of dispensing and return;
- Record of all adverse events and other safety parameters (start and end date, and including causality and severity);
- Concomitant medication (including start and end date, dose if relevant; dose changes);
- Date of study completion and reason for early discontinuation, if it occurs.

